## Abstract

**Background:**

Suboptimal physical activity levels and tolerance, poor motor skills and poor physical health are demonstrated in children with Autism Spectrum Disorder (ASD). We speculate that social interaction and communication deficits in children with ASD are two major factors that hinder these children from actively participating in group physical activities. While previous studies have demonstrated that exercise intervention improves motor skills and behavioral outcomes in children with ASD, these programs tend to focus only on a single sport, which may not cater to the interests of different children with ASD. In this protocol, a game-based exercise training program designed by a multi-disciplinary team (pediatrics, physical education and psychology) will be implemented by front-line healthcare providers trained following the train-the-trainer (TTT) model and subjected to validation.

**Method:**

Using a randomized controlled trial design, the effectiveness of the game-based exercise program will be examined for 112 young children with ASD. These children were randomly assigned to two groups, which will be tested and trained in either one of the two arms of the waitlist conditions (control and intervention). The assessment of physical and psychological traits will be conducted at baseline (pre-test), at 16-weeks (post-treatment) and at 32-weeks (follow-up) of the program.

**Discussion:**

Most of the interventions designed for ASD children target either their psychological traits or physical conditions, without bridging the two states. With the recognition of bidirectional relations between mental and physical health, the present game-based exercise program which includes multiple level of difficulties was developed to equip ASD children with the necessary skills for engaging in sustainable team sports or even professional sport training. The program, if effective, will provide an entertaining and engaging training for whole-person development among children with ASD.

**Trial registration:**

This study is registered with the Chinese Clinical Trial Registry (ChiCTR-IOR-17011898). Registered 6^th^ July 2017.

## Background

The prevalence of Autism Spectrum Disorder (ASD) is increasing globally, and Hong Kong is of no exception [1]. In Hong Kong, the average prevalence of ASD was 16.1 per 10000 for children less than 15 years old from 1986 to 2005 [2]. Since then, new cases of ASD in Hong Kong children have increased remarkably, with 184% new cases reported from year 1997 to 2005 [3]. ASD is characterised by a number of neurodevelopmental-based impairments, including social interaction and communication deficits, repetitive and stereotypical behaviours and interests [4]. Apart from the core diagnostic symptoms, many ASD children may also have impairments in the cognitive-behavioural and perceptuomotor domains, motor function, as well as static and dynamic balance [5]. Because of these social and behavioural deficits, children with ASD typically present with decreased physical activity levels, sedentary lifestyle, and lower exercise tolerance relative to their typically developing counterparts [6, 7]. Motor skills in ASD children are typically poorly developed or delayed [8], and sadly, ASD in children is often comorbid with developmental coordination disorder [9]. These deficiencies in motor control, coupled with a lack of engagement in physical activity, make individuals with ASD prone to chronic diseases [10]. Obesity, for example, is highly prevalent amongst children with ASD [5, 10].

Five previous reviews have been conducted regarding the impact of physical activity or exercise intervention on children and adults with ASD [11–15] and all report promising results. Apart from improvements in motor skills, improvements on numerous behavioural outcomes including stereotypic behaviours, social-emotional functioning, cognition and attention have also been reported in children after physical activity or exercise intervention [12, 13]. Vigorous exercise was reported to have a more pronounced effect than milder less strenuous exercise [12, 16–19]. However, studies that use a randomized controlled trial (RCT) design [20–24] or focus on younger children (4 to 6 years old) [25] are very limited. Among the existing studies with children, jogging and swimming are the two most common exercises selected as the core component of the intervention. Other exercise items include horseback riding, martial arts, resistance training, yoga and dance [12, 13].

To encourage children with ASD to engage in physical activity, more support for these children and their parents is necessary. The present study implements a multidimensional training program that incorporates elements such as aerobic and resistance training, fundamental movement skills, speed, plyometric and agility development, etc. to benefit these children, especially the younger age group [26]. The multidimensional design of the exercise training program aims to strengthen the fundamental physical conditions that support a variety of sports and exercise activities. The incorporation of multiple sport skills also prevents the risk of overuse injuries when performing a single exercise training in the long run [26]. To the best of our knowledge, no studies of exercise training program with multidimensional training elements in young children with ASD have been published. Thus, our research team consisting of experts from multiple disciplines such as pediatrics, psychology, sport sciences and physical education designed the present game-based exercise program to provide more comprehensive support for children with ASD. Furthermore, we adopted a train-the-trainer (TTT) model to facilitate the sustainable use of the program in the community. Following this model, we trained a group of front-line healthcare providers from non-governmental organizations, who in turn implemented the training on children.

The training program in the present study was designed specifically to cater to children. The exercise activities were presented to children in the form of games, with each game carefully designed such that it has elements that train both physical and mental abilities. In addition, the games were designed to include various levels of difficulty so that trainers can administer the game at appropriate levels for children. This may also motivate children to progress to higher levels in the course of the training. In this study proposal, the impact of our exercise program on the physical and psychological conditions of children with ASDs was hypothesized. The success of the program will also provide support for the feasibility of the train-the-trainer model.

### Aims and hypotheses

The first aim of this study was to test the effectiveness of a supervised game-based exercise training program in promoting motor skills and physical fitness, as well as reducing stereotypical and maladaptive behaviours in preschool children with ASD. These physical abilities served as the primary outcomes, while social and language skills were measured as secondary outcomes. Secondly, this study also aimed to evaluate the efficacy of this program as implemented by front-line healthcare providers through the train-the-trainer approach. We hypothesized that when compared to the waitlist control group, the exercise training program will lead to (1) increased motor skills and physical fitness and reduced stereotypical and maladaptive behaviours in preschool children with ASD; thus providing evidence for (2) the feasibility and sustainability of this supervised tailor-made exercise training program for young children with ASD following the train-the-trainer approach.

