#### Children’s physical fitness

Children’s physical fitness will be assessed by a battery of tests: the PREFIT battery [31], which comprises the measurements of body weight and height and waist circumference to assess anthropometry, the PREFIT 20 meter shuttle run test [32] for cardiorespiratory fitness, handgrip strength and standing long jump tests for muscular strength of upper limbs and lower limbs respectively, 4 x 10 meter shuttle run test for speed-agility and one-leg stance test for balance [31]. In addition, the upper limb power [33] of each child will be assessed.

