### Statistical methods

Raw data of all key variables will be tested for normality prior to analysis. Analyses will be done using repeated-measures Analysis of Variance (ANOVA) and mixed models as the primary design. Multiple imputations will be used for missing observations at post-intervention and 3-month follow-up. Reporting of the results of the study will be in accordance with the CONSORT 2010 Statement [59].

In the aforementioned analysis plan it is assumed that children will play the game individually and the data will not be clustered. However, in cases of clustered data due to the formation of groups in which several children play the game in the same room, the analyses will be conducted in MPLUS 6.11 [60].

First, the two groups will be compared with respect to age, gender, nonverbal intelligence (IQ), and CAST and AQ-Child severity score in order to assess the comparability between them with independent samples t-tests. Baseline descriptors that differ significantly are taken into account in the following analyses.

To investigate the effectiveness of the TTT program, we explore both within-subject effects (changes within children across time) and between-subject effects (changes between children in the control condition versus the intervention condition). ‘Time’ is the within-subject variable, with three levels: T1 (baseline), T2 (effect), and T3 (follow-up). ‘Condition’ is the between-subject variable, with two levels: intervention condition and control condition. The tasks we employed will all yield continuous data. We corrected for multiple testing using Bonferroni correction. Statistical analyses are performed using SPSS 24.0 statistical software (SPSS) and are two-tailed, with a level of significance of α = 0.05.

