## Discussion

The prevalence of Autism Spectrum Disorder is increasing worldwide. However, social and behavioural deficits among children with ASD make interaction with peers difficult, and such physical and social constraints have shown to reduce the physical activity level in children with ASD. Sedentary lifestyle not only affects a child’s general health and family dynamics but may further isolate and deprive the child’s social adaptive function and skills. The design of this protocol is a randomized controlled design, which focuses on young children (4 to 6 years old) with ASD. The protocol also includes a training manual for front-line healthcare providers, which allows them to implement the training to young children with ASD in community settings after they have equipped through the train-the-trainer workshop.

The design of the training program is different from previous studies in that a multidimensional training program which includes a number of training elements is adopted. This allows children to build up their physical conditioning needs for a variety of sports and activities. If this training program is shown to be effective, it can be promoted as one of the interventional strategies among young children with ASD, to equip them life skills which are necessary for enjoying leisure and sport, in turn, enhance physical fitness and psychological well-being. The implementation of the training program by front-line healthcare providers can facilitate the program to be used sustainably in the community.

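### The primary outcome set and the rule for success are not fixed, so a mixed result on the fitness tests could be read either way after the data are seen

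*Protocol article*

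**What the plan says.** Aims and hypotheses sets out the first aim: to promote motor skills and physical fitness and to reduce stereotypical and maladaptive behaviours. The next sentence reads "These physical abilities served as the primary outcomes, while social and language skills were measured as secondary outcomes". Hypothesis (1) again runs the two domains together: "increased motor skills and physical fitness and reduced stereotypical and maladaptive behaviours in preschool children with ASD".

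Under Children's physical fitness, fitness "will be assessed by a battery of tests: the PREFIT battery [31], which comprises the measurements of body weight and height and waist circumference". The performance tests are the 20 m shuttle run, handgrip, standing long jump, 4 x 10 m shuttle run and one-leg stance. A sixth, the overhand throw, is added: "In addition, the upper limb power [33] of each child will be assessed". No lead test and no summary score is named, and the Measurements section does not label any instrument as primary.

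Statistical methods gives one sentence on multiplicity, "We corrected for multiple testing using Bonferroni correction", and says that the analyses "are two-tailed, with a level of significance of α = 0.05". The family and the number of tests are not given. The Discussion then attaches a single global consequence to the result: "If this training program is shown to be effective, it can be promoted as one of the interventional strategies".

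**The concern.** Two things that a protocol should settle are left open.

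- **Membership.** The phrase about physical abilities refers back to a sentence that also contains behaviours, which are not physical abilities. It is unclear whether the behavioural outcomes are primary. It is also unclear whether height, weight and waist count, since they sit in the same battery as the performance tests.
- **Success.** Nothing says whether one, some or all of the primary variables must be significant before the programme is called effective.

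The Bonferroni sentence does not fill the gap. It follows directly on the description of the Time and Condition factors, so even its family is open: fitness tests, all outcomes, or time-point contrasts.

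The stake is the trial's headline answer. If, say, two of six tests pass, one author could report that the programme works and another that the hypothesis failed, and neither would depart from the text.

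**Working it through.** **Membership, from the text.** Counting only performance tests gives K = 6. Adding height, weight and waist gives K = 9. Adding behavioural outcomes gives a larger, unstated number. All are compatible with the wording.

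**Size of the problem.** The question is how often a trial would give a mixed result, meaning at least one but not all tests pass.

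Inputs from the protocol article:
- 50 children per arm after drop-out and an expected difference of 0.90 SD (Sample size calculation)
- two-sided alpha of 0.05 and Bonferroni (Statistical methods)
- six performance tests (Children's physical fitness)

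Assumptions, because the document gives no figure:
- the family is the six tests
- the true effect is the same on every test
- between-test correlation is 0.2, 0.5 or 0.8
- children are independent

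**Which effect size.** The protocol's 50 per arm does not reproduce from 0.90 SD: a two-sample t-test at 80% power needs 21 per arm. The effect for which 50 per arm gives 80% power is 0.566 SD. That mismatch is a separate matter, but it is the reason for showing both effects here.

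**Power per test.** The expected z is d / sqrt(2/50), and the Bonferroni critical value is z(1 − 0.025/6) = 2.638.
- d = 0.566: expected z = 2.83; power = Φ(2.83 − 2.638) = Φ(0.192) = 0.576
- d = 0.90: expected z = 4.50; power = Φ(4.50 − 2.638) = Φ(1.862) = 0.969

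**Hand check at zero correlation, d = 0.566.** Any test passes: 1 − 0.424^6 = 0.994. All pass: 0.576^6 = 0.037. Mixed: 0.994 − 0.037 = 0.957. Simulation at zero correlation also gives 0.957.

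**Simulation, six equicorrelated z-statistics, 400,000 draws, Bonferroni:**

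| True effect on every test | Correlation | At least one passes | All six pass | Mixed |
|---|---|---|---|---|
| 0.566 SD | 0.2 | 97.1% | 9.4% | 87.7% |
| 0.566 SD | 0.5 | 90.2% | 20.2% | 70.0% |
| 0.566 SD | 0.8 | 78.9% | 34.5% | 44.4% |
| 0.90 SD | 0.2 | 100.0% | 84.1% | 15.9% |
| 0.90 SD | 0.5 | 100.0% | 87.4% | 12.5% |
| 0.90 SD | 0.8 | 99.5% | 91.5% | 8.0% |

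With K = 9 and correlation from 0 to 0.7, mixed results occur in 99.6% to 63% of trials at 0.566 SD and in 32% to 15% at 0.90 SD.

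**Holm against Bonferroni, K = 6.** Holm compares the ordered p-values with 0.05/6, 0.05/5, …, 0.05. Its first threshold equals Bonferroni's and the later ones are looser, so it rejects everything Bonferroni rejects while holding the same family-wise error. Average power per test rises from 58% to 67–69% at 0.566 SD, and from 97% to about 99% at 0.90 SD.

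**Composite, K = 6.** The mean z-score of the six tests, tested once at 0.05, has 96% power at correlation 0.5 (99.8% to 87% for 0.2 to 0.8) if every test improves by 0.566 SD. If only one test improves by that amount, at correlation 0.5 it has about 9% power, against 59% for at least one Bonferroni rejection.

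**The case against.** **A formal contradiction.** A reader might infer that the hypothesis, joined by the word 'and', requires success on every component, that Bonferroni implies success on any one, and that the two therefore contradict each other. The document does not support this. The 'and' can be ordinary prose listing expected effects. Bonferroni also serves separate per-test conclusions with family-wise error controlled, and does not commit the trial to a rule that one success is enough. Neither rule is stated, so what stands is an omission.

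**An effective programme usually missed.** A reader might also infer that a truly effective programme would usually be declared unproven, because all six tests pass Bonferroni in only about 9% to 35% of trials. That holds only at the back-solved 0.57 SD and only if all six must pass. At the protocol's stated 0.90 SD, all six pass in about 84% to 91%, which reverses the claim.

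**Detail left to the analysis plan.** The exact Bonferroni family may sit in a fuller document that is not shown, and this is fair for the number of tests. It does not cover the primary outcome itself: the article does define it, and does so in a way that leaves membership open.

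**Bonferroni is valid.** This is correct. Moving to Holm is a free gain in power, not the repair of an error.

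**Conclusion.** The point holds as an unfixed primary set and an unstated success rule. That conclusion rests on the text alone and needs no simulation. The practical size does rest on assumptions: with six tests, 50 per arm, equal effects and correlation 0.2 to 0.8, an outcome whose verdict depends on the missing rule arises in about 88% to 44% of trials at 0.57 SD and in about 16% to 8% at 0.90 SD. The ambiguity is therefore minor if the protocol's optimistic effect is true, and likely to decide the headline if effects are nearer the size for which 50 per arm gives 80% power. It should be settled before outcome data are examined. The figures do not show that the hypothesis and the correction are incompatible, or that a composite endpoint is needed.

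**What to change.** In Aims and hypotheses and in Statistical methods:

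1. Name the primary family and its time point, for example the between-arm differences in the six performance tests at T2, with height, weight and waist descriptive.
2. State whether the stereotypical and maladaptive behaviour outcomes belong to that family and, if not, where they go.
3. Replace Bonferroni with Holm over the named family at two-sided 0.05.
4. Word the conclusion for each test that passes, instead of one global statement that the programme is effective. This step removes the ambiguity of a mixed result; Holm alone does not.
5. Keep social and language outcomes as a separate secondary family.

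A single primary endpoint, such as the mean standardised score of the six tests with the timed run reversed, is open to the sponsor. It gains power if all tests improve and loses most of it if only one does, so it is a choice and not a correction.

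The cost is wording only, with no new data or children. Holm has no power cost relative to Bonferroni; its one inconvenience is that matching simultaneous confidence intervals are less simple to construct. Study design places the trial in recruitment, so at that stage the change could be made before any outcome comparison.

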## Methods/Design

### Study design

This is a randomized controlled trial (RCT) study registered with the Chinese Clinical Trial Registry (ChiCTR-IOR-17011898). The study is ongoing and is during the subject recruitment phase (August to Sept, 2017). Community centers within a local non-government organization were recruited. The recruited ASD children will be randomly assigned to either the treatment group or a wait-list control group using the *simple randomization* method with the employment of a toolbox provided in MS Excel, to be performed by the first author. The exercise training program will be offered to children in the wait-list control group after the posttest of the treatment group (Fig. 1).

**Fig. 1 Fig1:**
[figure not shown]
Flow chart of the study design

### Participants

With an agreed partnership with a local non-governmental organization (NGO), children were recruited through the community centers within this NGO. Front-line healthcare providers (mainly social workers) from these centers was recruited as trainers to implement the supervised exercise training program for children with ASD after completing the train-the-trainer workshop. Children aged 4 to 6 years old with a formal diagnosis of either Autism, Autistic features, Autism Spectrum disorder, Asperger Syndrome, Pervasive Developmental Disorder by Developmental Paediatricians or Clinical Psychologists based on the Fourth Edition of the Diagnostic and Statistical Manual of Mental Disorder (DSM-IV) were invited to join the study[27]. Children with underlying congenital abnormalities or other diseases that limit them to participate in daily physical activities was excluded from the study.

### Intervention

The exercise program is a 16-week game-based exercise training program. Two sessions will be run each week to form a total of 32 sessions over 16 consecutive weeks. Each session will last for an hour. Six to eight stations will be set up and children will be instructed to finish the exercises in all stations one after another in a fixed order. After finishing a circuit of the prescribed exercises in a particular session, children will be guided by front-line healthcare providers to complete another circuit of the prescribed exercises. Three circuits of prescribed exercises are expected to be finished within a training session. The exercises in different stations are designed to train various muscle groups or fitness components. Exercise stations within an exercise session will be changed biweekly according to the children’s progression. Parents of the participating children are encouraged to join the class and accompany their child during the training session.

The program encapsulates physical, social, linguistic and communication skills training aspects, and can be divided into three phases (about 5 to 6 weeks for each phase) to achieve different targets:

#### Phase I

To establish trust between the children and their coaches, and to allow children to get used to the training regime of the program. Paired group activities are included in this phase.

#### Phase II

To promote cardiopulmonary fitness and muscular strength, and to increase the range of movement of large joints. Paired group activities are included in this phase, with increased exercise intensity of each session.

#### Phase III

To reduce maladaptive behaviors amongst the children and to improve their attention span. Exercise intensity for each session is the highest among three phases. Large group activities are included in this phase.

